### Informed consent

Participants are recruited at the Department of Hematology, The First Affiliated Hospital of Zhejiang Chinese Medical University (Zhejiang Provincial Hospital of Chinese Medicine). Hematologists will provide us with lists of AA patients who are scheduled for HSCT every day. [name] apply the inclusion and exclusion criteria to screen and subsequently recruit the patients for participation. Once patients are deemed eligible to participate, they will sign a written version of the informed consent form with voluntary informed consent, with no study procedures taking place until consent has been obtained. At T0 visit, a member of the study team will confirm eligibility.

### Intervention

The intervention group received a structured exercise rehabilitation program, which was mainly developed by our team through preliminary literature research and by inviting experts in the relevant fields (including hematologists, nurses, and rehabilitation therapists) [24]. The exercise rehabilitation was divided into 3 phases according to the different periods of the patient’s transplantation; each phase involved warm-up, formal, and finishing exercises, and was tailored according to the strength of each participant.Phase 1: Exercise rehabilitation in the transplantation module (neutrophil and platelet engraftment to out of the transplantation module). Considering that the patient was weak in the early post-transplantation period, exercises in this phase were mainly bed and bedside activities. The warm-up exercises were mainly lip reduction-abdominal breathing with progressive relaxation exercises (involving hand muscles, arm muscles, hip muscles, thigh muscles, calf muscles, and toe muscles), for exercising the muscles of the whole body; the aerobic exercises in formal exercises were mostly performed with bed-side bicycles; the resistance exercises were mainly bed or bedside elastic band exercises performed by the patient (involving biceps, triceps, psoas major, abdominal, gluteal and foot muscles); and the finishing exercises wrapped up with progressive relaxation exercises.Phase 2: Exercise rehabilitation in the hematology ward (during admission to the general ward).

Patients who were transferred from the transplant module were in better condition than before, so it was appropriate to increase the intensity of exercises and move from bed to floor. The warm-up exercise included 6 movements (including head exercise, shoulder circuit, chest expansion, waist circuit, knee circuit, and wrist and ankle exercises) to avoid injury during exercise; the aerobic exercise options for formal exercises included Baduan Jin and Tai Chi; the resistance exercise was a stretch band exercise consisting of 8 movements (more difficult than before); and the finishing exercise was a relaxing stretch of the whole body in 8 movements from head to toe.Phase 3: Out-of-hospital exercise rehabilitation (post-discharge to 100 days post-transplantation).

The patient continued the exercise pattern of phase 2. Meanwhile, after taking into account the patients’ return to society, exercise modalities such as cycling, jogging, brisk walking and stair climbing were added to the aerobic exercises. In addition to stretch band exercises, patients were recommended a suitable form of exercise based on the definition of 3 to 6 metabolic equivalents (MET) for moderate-intensity exercises released by the United States Department of Health and Human Services (HHS) [25].

Videos prepared by researchers were used to teach exercises of all movements. Patients could broadcast the videos on TV or mobile phones. As recommended by the experts, the warm-up exercises and finishing exercise should last for 5–10 min each time. Aerobic exercises were performed twice a week for 20–25 min. Resistance exercises were implemented thrice a week for 15–20 min, and the appropriate Thera-band elastic band was selected according to the patient’s platelet count [26]: (1) PLT < 20 × 10^9^/L: resistance exercise was not recommended; (2) 20 × 10^9^/L ≤ PLT < 30 × 10^9^/L: yellow elastic band (3.0 lbs); (3) 30 × 10^9^/ L ≤ PLT < 50 × 10^9^/L: yellow or red elastic band (3.7 lbs); (4) 50 × 10^9^/L ≤ PLT < 150 × 10^9^/L: red elastic band (3.7 lbs); and (5) PLT ≥ 150 × 10^9^/L: red or green elastic band (4.7 lbs) was recommended.

The exercise intensity was monitored using the target heart rate (THR) combined with the Rating of Perceived Exertion (RPE) Scale. To be specific, exercise intensity was targeted between 50 and 75% of heart rate (HR) reserve, in which THR = [(max HR − resting HR) × % intensity] + resting HR, where max HR = 220-age (for female) or 205-age (for male). Participants also used the RPE scale score of 12 ~ 14 points as the target exercise intensity. They followed the principle of gradual progression in the process of exercises.

Participants in the control group were randomized to usual care receiving usual care treatment according to the Chinese Expert Consensus on the Diagnosis and Treatment of Aplastic Anemia [27], including pre-HSCT workup, conditioning regimen, management of early issues, and late complications post-HSCT. In addition, access to educational materials on allogeneic bone marrow transplant was published by UpToDate [28]. Receiving health education and encouragement related to exercise, but there is no standardized program or specific requirements.

#### Criteria for discontinuing or modifying allocated interventions

This study allows patients to withdraw from the research voluntarily, and if a participant experiences an adverse reaction related to the study during the treatment process, the clinical doctor can exclude them from the study. If participants withdraw due to negative effects, the clinical doctors will assess whether they require further treatment.

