### Variables and measurement instruments

Sociodemographic and clinical variables: To characterize the samples, sociodemographic and clinical data were extracted from the participants, containing age, gender, marital status, educational level, professional/employment status, household income, duration of AA, medication, and type of treatment.QoL: it was measured using the validated European Organization for Research and Treatment of Cancer Quality of Life Questionnaire-Core 30 (EORTC QLQ-C30) [29]. This questionnaire consists of 30 items covering 15 domains, which reflect the patient’s physical, role, emotional, cognitive and social functioning, a global quality of life domain, together with fatigue, nausea and vomiting, pain, dyspnea, insomnia, loss of appetite, constipation, diarrhea, and financial difficulties. All items were rated on a 4-point response scale ranging from 1 (not at all) to 4 (very much) points, except for the two items measuring general health and QoL (summarized as global QoL) that were rated on a visual analogue scale from 1 ~ 7 points. All scales were transformed to a percentile scale from 0 ~ 100 points, with the higher scores representing better functioning and global QoL, whereas the higher scores on the symptom scales indicated the higher levels of symptoms or problems.Upper limb muscle strength: it was assessed by measuring the grip strength using a hand dynamometer (EH101, Camry, China) [30]. To be specific, the participant was asked to sit upright in a chair and place the feet on the floor. The shoulder of the limb to be tested was kept adducted and neutral for rotation, with the elbow being flexed at 90°, wrist extension between 0 and 30° and ulnar deviation of 0 ~ 15°. The left and right hands were alternately measured thrice each and the average value was taken as the grip strength of the participant. During the test, the participants were constantly verbally encouraged to use their maximum strength.Lower limb muscle strength: it was evaluated with the Five Times Sit to Stand Test (FTSST) [31]. In brief, participants were required to sit in an armless chair at a standard height (45 cm) and tested on the duration of 5 sit-to-stand movements. In the test procedure, the participants were asked to stand upright with their upper body, with arms crossing over the chest and feet flat on the floor. Participants were asked to stand up completely without using their upper limbs and then sit down again.Fatigue: it was measured with the Brief Fatigue Inventory (BFI) questionnaire [32]. The BFI questionnaire covers 10 items. The first item determines whether there has been abnormal fatigue over the last week using a “yes” or “no” option. The other items determine the current level of fatigue and the impacts of fatigue on general activity, mood, walking ability, relationships with others, and enjoyment of life. Each item is based on a 0–10-point scale, with a score of 0 representing the best state and no fatigue, whereas that of 10 indicating the worst state of fatigue. Participants were asked to mark their answers to each question based on their perceived level of fatigue, and the overall fatigue level was measured by calculating the total score of items 2 to 10 divided by 9. To be specific, a score of 0 meant no fatigue, while those of 0.1 ~ 3.9, 4 ~ 6.9, 7 ~ 9.9, and 10 were indicative of mild, moderate, severe, and very severe fatigue, separately.Hematological indicators: These indicators included platelet (PLT), neutrophil (Neu), hemoglobin (HB), and reticulocyte (Ret) counts in the peripheral blood of participants.Exercise adherence: it was assessed by the exercise attainment rate, which was the number of people attaining the standard/total number of people × 100%. Exercise attainment was defined as exercising at least thrice a week for 30 min or longer (or ≥ 10 min each time for a cumulative total of 30 min).Adverse events: the proportion of adverse events occurring during the study period was determined.

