### Randomization and blinding

Eligible participants will be randomly divided into two groups in a 1:1 ratio. Randomization will be conducted using an automated permuted block. The block size will not be disclosed to study staff who are enrolling patients or assigning interventions. The computer-generated randomization sequence will be kept by an independent researcher not involved in the exercise rehabilitation assessment and will be kept in a sealed envelope. Since the intervention in this study is exercise rehabilitation, the interventionists and participants will not be blinded. Participants will be informed of the intervention after completing all baseline assessments. Outcome assessors will be blinded, so unblinding will not occur. And participants will be told not to reveal the intervention they received while performing the outcome measure.

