### Safety/harms

Any adverse events that occur will be monitored and recorded throughout the trial. Potential minor adverse events that can be expected may be fatigue, tachycardia, dizziness, or blurred vision, which can be minimized mainly through assessment and monitoring. Based on the patient’s adverse events, a professional will assess and decide whether further treatment is required. If adverse events are reported, they will be collected and categorized according to expectedness, seriousness, severity, and potential relevance to the study. This information will then be relayed to the study’s steering committee, and the ethics committee will be informed accordingly.

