## Statistical analysis

SPSS26.0 was adopted for statistical analysis of data. Missing data were filled in using the Last observation carried forward (LOCF) and statistical analysis was conducted following the intention-to-treat (ITT) principle. Statistical tests were carried out with two-sided tests and *P* 0.05 was considered a statistically significant difference. Gender, education level, marital status, exercise adherence, and incidence of adverse events were described as frequencies and percentages. In the meantime, age, duration of AA, time to HSCT and QoL, muscle strength, fatigue, PLT, Neu, HB, and Ret counts were described as means and standard deviations if they conformed to normal distribution, or median if they conformed to non-normal distribution. The chi-square test or *t-*test was employed to compare differences between the intervention and control groups. Taking into account the potential variations in age, gender, and education level, analysis of variance (ANOVA) was conducted to assess the development of outcomes over time. Additionally, repeated measures analysis was used to analyze scores at baseline and follow-up scores of all measures.

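### The adverse-reaction rule takes participants out of the study rather than only out of the exercise, mostly in one arm, which undermines the stated intention-to-treat analysis

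*Protocol article*

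**What the plan says.** The section on criteria for discontinuing or modifying allocated interventions allows voluntary withdrawal. It adds that "if a participant experiences an adverse reaction related to the study during the treatment process, the clinical doctor can exclude them from the study". It does not distinguish stopping the exercise from leaving the trial, and it does not say whether an excluded participant is still assessed.

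The Statistical analysis section says that "statistical analysis was conducted following the intention-to-treat (ITT) principle", with missing values filled by LOCF. It does not say whether an excluded participant stays in the analysis set.

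Three other places bear on the point:
- Randomization and blinding: "the interventionists and participants will not be blinded". Only outcome assessors are blinded.
- Variables and measurement instruments: adverse events are an outcome, for which "the proportion of adverse events occurring during the study period was determined".
- Safety/harms: "Potential minor adverse events that can be expected may be fatigue, tachycardia, dizziness, or blurred vision".

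**The concern.** The heading of the section concerns the intervention, but the rule acts on study membership. Its trigger is a reaction related to the study. Only the intervention arm follows the structured aerobic and resistance programme. That programme also brings a daily log with an adverse-event entry, supervision in the first two phases, and daily check-ins and weekly calls in the third. Reactions of this kind are therefore both more likely to occur and more likely to be noticed in that arm, and nothing in the article shields the attribution from knowledge of allocation.

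The removal may also be related to outcome. Fatigue is listed as an expected adverse event, and it is also a secondary outcome (BFI) and a domain of the EORTC QLQ-C30, the primary instrument. A participant could leave the study because of something the trial is meant to measure.

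At stake are the T1 to T3 scores of participants who react badly to the exercise, and any adverse events they have after exclusion. Data that were never collected cannot be recovered by analysis.

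**Working it through.** **The plan's own figure.** Inputs from the Sample size section: SD 17.6, difference 12.3, two-sided alpha 0.05, power 0.80.

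n per arm = 2 × (1.960 + 0.842)² × (17.6 / 12.3)² = 2 × 7.85 × 2.047 = 32.1, rounded up to 33.

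This reproduces the stated 33. The 20% allowance gives 33 / 0.8 = 41.25, against the stated 41. The sample size does not depend on this point. The 12.3 and 17.6 serve below only as a yardstick.

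**What exclusion means for the analysis.** The article allows two readings. It gives no exclusion rate, so the rates and deficits below are assumptions.

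*Reading A: excluded participants are left out of the analysis.* Let f be the fraction of the exercise arm excluded and d the amount by which the retained mean at T3 exceeds the mean the excluded would have had. The full-arm mean is the retained mean minus f × d, so the analysed mean is too high by f × d.
- f = 0.10 (about 4 of 41), d = 15: 0.10 × 15 = 1.5 points; 1.5 / 12.3 = 12% of the planned effect.
- f = 0.20 (about 8 of 41), d = 15: 0.20 × 15 = 3.0 points; 3.0 / 12.3 = 24%.

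The effect on type I error, with no true difference, exclusion in the exercise arm only and SD 17.6, uses b = f × d in SD units and SE = √(1/41 + 1/(41(1 − f))). The rejection probability is P(Z > 1.96 − b/SE) + P(Z < −1.96 − b/SE).

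| f | d (SD) | bias (points) | type I error |
|---|---|---|---|
| 0.05 | 0.5 | 0.44 | 0.051 |
| 0.05 | 1.0 | 0.88 | 0.056 |
| 0.10 | 0.5 | 0.88 | 0.056 |
| 0.10 | 1.0 | 1.76 | 0.073 |
| 0.20 | 0.5 | 1.76 | 0.071 |
| 0.20 | 1.0 | 3.52 | 0.137 |

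A deficit of 15 points is 15 / 17.6 = 0.85 SD, inside this range.

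*Reading B: excluded participants are kept, filled by LOCF.* The arm mean now shifts by f × (carried score − true T3 score). Suppose the planned values hold at T3, so that the exercise arm scores 56.3 + 12.3 = 68.6 and an excluded participant would have scored 68.6 − 15 = 53.6. A carried score above 53.6 favours exercise and one below it works against exercise. For example, with f = 0.10:
- carried score 63.6: 0.10 × (63.6 − 53.6) = +1.0 point;
- carried score 43.6: 0.10 × (43.6 − 53.6) = −1.0 point.

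The article gives no T0 or T1 quality-of-life values. Its Intervention section describes patients as weak early after transplantation and better once they leave the module, so a low carried score is plausible. A participant who deteriorates after the reaction gives the opposite case. The sign cannot be fixed from the document.

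**Adverse events.** The event that triggers exclusion has already happened and is recorded. What can be lost is any later event, and more of these in the arm with more exclusions.

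**The case against.** A reader might infer that the rule can operate only in the exercise arm. The text does not support that. It refers to any participant. Controls also have some exposure: "Receiving health education and encouragement related to exercise, but there is no standardized program or specific requirements". Both arms do the same effort tests, including a grip test in which "the participants were constantly verbally encouraged to use their maximum strength". Predominantly is the word the document supports.

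A reader might also infer that the rule defeats ITT outright. The article does not say that exclusion from the study is exclusion from the analysis. Read with the LOCF rule, an excluded participant could stay in the set as randomised, and analysis-set detail is often left to a fuller document. This stands, and it means the Reading A figures describe only one possible analysis. It does not rescue the rule: under Reading B membership of the set survives, but the outcome analysed is an earlier score, substituted more often in one arm.

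Two further replies have weight. The power to exclude is discretionary and the expected events are called minor, so exclusions may be few. And Safety/harms says events are recorded throughout the trial, so it would go too far to say that the triggering harm is missed.

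**Conclusion.** The point holds as an undermining of ITT, not a defeat of it. The article states a rule that takes participants out of the study after a study-related reaction, in an open-label setting, with the burden falling mainly on the exercise arm. Nothing in it keeps their outcomes in view.

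- If they are dropped, the analysis is not ITT, and it favours exercise provided they would have done worse: 1.5 to 3.0 points at 10 to 20% excluded and a 15-point deficit.
- If they are carried forward, the bias may go either way.
- On both readings, outcomes and later adverse events can be lost unequally between arms.

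The size rests entirely on assumed rates and deficits. At 5% excluded the bias is below 1 point even with a deficit of 1 SD. A flat claim that the rule biases the trial in favour of exercise would go beyond the document.

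**What to change.** Reconcile the section on discontinuing or modifying interventions with the Statistical analysis section by separating two events: stopping the allocated intervention and leaving the study. Leave the clinical trigger and the doctor's decision exactly as they are. Add that a participant whose intervention is stopped:
- remains in the study;
- is assessed at T1, T2 and T3 and followed for adverse events, unless consent to follow-up is withdrawn;
- is analysed in the arm to which they were randomised.

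Record stopping of the intervention and withdrawal from follow-up as separate items, each with date and reason.

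The cost is a small amendment, which the protocol's own rule sends back to the ethics committee, and one data field. Extra patient burden is slight: T1 and T2 are inpatient assessments, and T3 takes place in the hematology ward or clinic. The Trial status section expects completion by August 2024, so the amendment helps only participants not yet past T3. For anyone already excluded, the report should give numbers and reasons by arm.

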#### Adherence

In addition, an exercise rehabilitation log was issued to the participants during the exercise period. The exercise log, which was required to be recorded faithfully each day, covered several aspects including type and duration of exercises, subjective exercise responses (like the assessment of pain, fatigue, emotional state, and distress), and adverse events. When no exercise was performed, the reason should be provided. The first two phases of exercise rehabilitation were supervised by the interventionists, while the third phase of out-of-hospital exercise rehabilitation was supervised by daily WeChat exercise punch cards and weekly telephone contact. The exercise rehabilitation program was from the participant’s neutrophil and platelet engraftment after transplantation (approximately 14 days post-transplantation) to 100 days post-transplantation.

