
### Participant timeline

The participant timeline is shown in Table 1.

**Table 1 Tab1:** Participant timeline

	STUDY PERIOD			
	Baseline	Post-allocation		
TIMEPOINT^a^	*t*_*0*_	*t*_*1*_	*t*_*2*_	*t*_*3*_
ENROLMENT:				
Eligibility screen	X			
Informed consent	X			
*Demographics*	X			
*Medical history*	X			
INTERVENTION:				
*[Intervention group]*		X	X	X
*[Control group]*		X	X	X
ASSESSMENTS:				
*[EORTC QLQ-C30]*		X	X	X
*[hand dynamometer]*		X	X	X
*[ FTSST]*		X	X	X
*[BFI]*		X	X	X
*[Number and volume of RBC and PLT transfusions]*				X
*[Hematological indicators]*		X	X	X
*[Recruitment rate]*				X
*[Drop-out rate]*				X
*[Exercise adherence]*		X	X	X
* [Adverse events]*				X

^a^***t***_***0***_: the neutrophil and platelet engraftment (± 1day); ***t***_***1***_: discharge from the transplantation module (± 1 day); ***t***_***2***_: hospital discharge (± 1 day); ***t***_***3***_: 100 days post-transplantation (± 5 days)

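### The only adverse-event tool described sits in the exercise programme, so the between-arm comparison is at risk of detection bias, mainly from hospital discharge to day 100

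*Protocol article*

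**What the plan says.** **Collection in the exercise programme.** The Adherence subsection sits under Intervention. It states that "an exercise rehabilitation log was issued to the participants during the exercise period", to be filled in every day. The content includes "subjective exercise responses (like the assessment of pain, fatigue, emotional state, and distress), and adverse events". Interventionists supervise the first two phases. The third, out-of-hospital phase "was supervised by daily WeChat exercise punch cards and weekly telephone contact".

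**Collection in the control arm.** The last paragraph of Intervention gives controls usual care, health education and encouragement to exercise, but "there is no standardized program or specific requirements". It describes no log, diary or scheduled call for them.

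**Status of the outcome.** Primary and secondary outcomes lists adverse events as a secondary outcome. Variables and measurement instruments defines the measure: "the proportion of adverse events occurring during the study period was determined". Statistical analysis describes adverse-event incidence by frequencies and percentages and provides chi-square or t-tests between the groups. Randomization and blinding states that participants and interventionists are not blinded.

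**Timing.** Three places differ:

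- Primary and secondary outcomes puts all outcomes at T0, T1, T2 and T3.
- Table 1 marks the row "Adverse events" at t3 only.
- Safety/harms says: "Any adverse events that occur will be monitored and recorded throughout the trial".

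**The concern.** A comparison of adverse-event proportions is fair only if both arms are asked the same questions, equally often and in the same way. Here the one instrument named is a daily record of a prescribed exercise programme, kept by people who also have regular contact with the study team. The general statement under Safety/harms applies to everyone, but it names no instrument, frequency or collector.

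That section expects minor events: fatigue, tachycardia, dizziness and blurred vision. Most of these are symptoms that come to light when a patient is prompted. If the exercise arm is prompted daily and the control arm is not, the exercise arm can show more events at the same true risk. Open-label participation could push the same way. The likely result is an apparent excess of mild events with exercise, in a trial meant to inform whether the programme is taken up in practice.

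**Working it through.** **1. Is there an arm-neutral tool?**

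| Source | Exercise arm | Control arm |
|---|---|---|
| Daily log with adverse events | Yes (Adherence) | None described; exclusion is inferred |
| Supervision, punch cards, weekly calls | Yes, for exercise supervision | None described |
| General monitoring (Safety/harms) | Yes, method not stated | Yes, method not stated |
| Inpatient observation, T0 to T2 | Yes | Yes |
| Scheduled QLQ-C30 and BFI | Yes | Yes |

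The arms differ only in the first two rows. While patients are in hospital, ordinary clinical observation covers both arms. After T2 it falls away, and the log and calls continue in one arm. The exposed window is therefore mainly T2 to T3.

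**2. How much could unequal capture matter?** The protocol article gives no adverse-event risk and no capture rate, so there is no stated figure to reproduce. Every risk and capture rate below is an assumption.

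Let p be the true proportion of participants with an event, equal in both arms. Let s1 and s0 be the shares captured in the exercise and control arms. Then:

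- observed proportions are p × s1 and p × s0;
- the spurious risk difference is p × (s1 − s0);
- the spurious risk ratio is s1/s0, whatever p is.

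With s1 = 0.90 and p = 0.50:

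| s0 | Exercise | Control | Difference | Ratio | False-positive rate |
|---|---|---|---|---|---|
| 0.90 | 45.0% | 45.0% | 0 | 1.0 | 5.9% |
| 0.75 | 45.0% | 37.5% | 7.5 points | 1.2 | 11.6% |
| 0.60 | 45.0% | 30.0% | 15 points | 1.5 | 29.8% |
| 0.50 | 45.0% | 25.0% | 20 points | 1.8 | 48.3% |

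The last column is the chance that an uncorrected chi-square test at two-sided 0.05 rejects. It comes from exact enumeration of two binomials with 41 participants per arm, the planned size. Across p from 0.30 to 0.70 and s0 from 0.75 to 0.50, it runs from 7.7% (p = 0.30, s0 = 0.75) to 75.5% (p = 0.70, s0 = 0.50).

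**3. Allowing for the inpatient period.** The lower s0 values overstate the problem if capture is equal in hospital. Suppose each affected participant has one event, half of the events fall before T2 with capture of 0.90 in both arms, and control capture after T2 is 0.60. Overall control capture is then 0.5 × 0.90 + 0.5 × 0.60 = 0.75. That is the second row: a ratio of 1.2 and a false-positive rate of 11.6%.

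**4. The timing statements.** Four rows of Table 1 are marked at t3 only: transfusions, recruitment rate, drop-out rate and adverse events. The first three are cumulative quantities, so the mark may mean an end-of-study tally. That reading agrees with Safety/harms. It still does not match the statement that every outcome is measured at T0 to T3, and the table does not say that the mark is a tally.

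**The case against.** A reader might infer that controls are asked about adverse events only at T3. The documents do not support that. It rests on one mark in Table 1, which may be a tally, and two other sections say otherwise.

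A reader might also state as fact that controls have no log. The Adherence text says only that participants receive it, and exercise adherence is listed as an outcome without restriction to one arm. An exercise-only log is the likelier reading, because the log records a prescribed programme and its supervision, but it remains an inference.

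The punch cards and calls are described as supervision of exercise, not as adverse-event collection. What stands is that they give one arm more occasions to mention a problem.

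Fatigue is prompted in both arms by the BFI and the QLQ-C30, and the latter also covers several other symptoms. Follow-up assessors are blinded. This narrows the gap, but the protocol article does not say that questionnaire answers count as adverse events, and dizziness, tachycardia and blurred vision are not among the QLQ-C30 domains it lists.

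It would go too far to say that the trial cannot judge safety. Events are to be classified by seriousness, severity, expectedness and relation to the study; serious events in transplant patients are unlikely to depend on a diary; and the logs inform safety within the exercise arm.

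Finally, a journal article may leave the case-report form to the full protocol. The absence of a form is not the point here. The point is that the one tool described is tied to one arm's programme, and that the stated schedules disagree.

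**Conclusion.** The concern holds as a risk of detection bias, not as demonstrated bias. It applies to mild, symptomatic events and chiefly to the period from hospital discharge to day 100. The probable direction is a higher observed proportion in the exercise arm. The size cannot be known from the documents: spurious risk ratios of 1.2 to 1.8 follow from assumed capture of 0.90 against 0.75 to 0.50, and the lower end is the more plausible if inpatient capture is equal.

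The conclusion rests on reading the log as exercise-arm only. If controls in fact receive it, most of the concern falls away and the text should say so. The mismatch in timing between the outcomes section, Table 1 and Safety/harms needs correcting in either case. The sample size is not affected.

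**What to change.** - Use one adverse-event form, asked with identical wording in both arms at T1, T2 and T3 by the blinded follow-up assessors. It should ask about symptoms without mentioning exercise, so that it does not reveal allocation.
- Base the between-arm comparison on that form plus hospital records.
- Report events found only in exercise logs or calls separately, as descriptive safety data for the exercise arm.
- State who receives the log. Reconcile Primary and secondary outcomes, Table 1 and Safety/harms; if the t3 mark is a cumulative tally, label it so.

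**Cost.** The visits already exist, so the burden is one short form and an amendment, which the protocol article says needs renewed ethics approval. Mild log-only events leave the between-arm comparison but are still reported. Some imbalance may remain, since keeping a daily log may help recall at T3. Recruitment was under way at publication; for participants already past a visit, only hospital records can serve as the common source, and the report should say how many they are.
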